## Abstract

**Background:**

Due to an ageing population in Australia there has been an increase in the number of older adults with subjective cognitive impairment (SCI), a self-reported decline in cognitive function associated with an increased risk of mild cognitive impairment and dementia. There is no current, recommended treatment for SCI; therefore, the effectiveness of a supplement approved by the Therapeutic Goods Association that has the potential to enhance cognitive function in an at-risk cohort should be tested. The primary aim of this proposed research is to determine the efficacy of 6 months of treatment with BioCeuticals Cognition Support Formula® (containing *Bacopa monniera* (brahmi), *Ginkgo biloba, Panax ginseng* and alpha-lipoic acid) on cognition in older adults with SCI (utilising the CogState® one card learning and identification tests as co-primary outcome measures of visual short-term memory and attention; mean speed (ms), accuracy (%), and total number of hits, misses, and anticipations) compared with placebo. The secondary aims are to assess an improvement in other cognitive domains (executive functioning, processing speed, and working memory), evaluate safety, adverse effects, and determine efficacy on mood, fatigue, and neurocognition. It is expected that improvements across the study timepoints in the co-primary outcomes in the active treatment group (compared with placebo) will be evident.

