### Statistical analyses and dissemination

For each participant in each group and at each timepoint the following data from the primary and secondary outcome measures will be assessed. For the CogState® detection, identification, one card learning, and one back tests, we will assess mean speed (ms), accuracy (%), and total number of hits, misses, and anticipations; for the Groton Maze test, we will assess the total number of errors; and for the mood (DASS-42, SHAI) and fatigue (FACIT-F) outcomes, we will assess subscale and composite scores. CogState® data that are not normally distributed will be transformed using logarithmic base 10 transformations. Generalised linear mixed models with a between-subject factor of group (treatment, placebo) and within-subject factor of time (baseline, midpoint, endpoint) will be conducted to assess differences in continuous co-primary and secondary outcome measures. Planned simple contrasts will be conducted to assess all timepoints (baseline vs. midpoint, midpoint vs. endpoint, and baseline vs. endpoint). To handle any missing data, analysis of last observation carried forward will be undertaken within the intention-to-treat analysis model. The premise of the intention-to-treat model includes all participants in the final analysis even if non-compliance, withdrawal, or deviation from the protocol occurs [38]. Due to the nature of drop-outs in clinical trials, this analysis will be carried out on all five primary and secondary outcome measures of cognition and secondary outcomes of mood (DASS and SHAI) and fatigue (FACIT-F).

All tests will be two-tailed, α = .05. MANOVAs and Pearson’s correlations may also be utilised for assessment of psychophysiological data depending on the outcome measures assessed. All data will be analysed using SPSS. Results from the trial will be presented publicly to the community through peer-reviewed journals and scientific conference presentations. Additionally, individual trial outcomes will be forwarded to participants, with their consent.

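### The blanket log10 rule for non-normal CogState data suits speed but not the error counts (undefined at zero) or accuracy (worsens left skew); the scale should be fixed per metric

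*Protocol article*

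**What the plan says.** All of this stands in the protocol article, chiefly under Statistical analyses and dissemination.

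- **Metrics.** For the detection, identification, one card learning and one back tests, "we will assess mean speed (ms), accuracy (%), and total number of hits, misses, and anticipations". The Background paragraph of the Abstract attaches the same list to the two co-primary tests: "mean speed (ms), accuracy (%), and total number of hits, misses, and anticipations) compared with placebo". A further CogState count is secondary: "for the Groton Maze test, we will assess the total number of errors".
- **Transformation.** "CogState® data that are not normally distributed will be transformed using logarithmic base 10 transformations". No metric is singled out, no offset is given, and no other transformation is named.
- **Model.** "Generalised linear mixed models with a between-subject factor of group (treatment, placebo) and within-subject factor of time (baseline, midpoint, endpoint") are named, and they "will be conducted to assess differences in continuous co-primary and secondary outcome measures". No distribution or link is stated.
- **Missing data and population.** "To handle any missing data, analysis of last observation carried forward will be undertaken within the intention-to-treat analysis model", and the intention-to-treat analysis "includes all participants in the final analysis even if non-compliance, withdrawal, or deviation from the protocol occurs".

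**The concern.** One rule covers three kinds of variable. Mean speed is a positive, continuous measurement, for which a log is a natural choice. Accuracy is a percentage capped at 100, and hits are limited by the number of trials. Misses, anticipations and Groton Maze errors are counts that can be zero.

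Two things then go wrong. For the error counts, log10(0) does not exist, and zero is the best score a participant can have. Low counts are also the data most likely to look non-normal and so to trigger the rule. For accuracy, the log is concave, so it stretches the lower tail. If the distribution is left-skewed, the prescribed remedy aggravates what it is meant to correct.

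The trigger is a further weakness. The scale of a comparison listed under the co-primary tests depends on how the observed data look. At stake are the size of the reported effect and the power on those metrics.

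**Working it through.** **Inputs.** The article gives the metrics, the rule, the model and LOCF, as above. It also gives 100 evaluable participants across two groups (Sample size section), hence 50 per arm. It states no figure for zero counts or for skew, so there is no figure of its own to reproduce here, and its sample size calculation does not bear on this point. Count means, dispersion, numbers of test trials and accuracy levels below are assumptions, shown as ranges.

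**1. How often zeros occur.** For a Poisson count with mean m, P(0) = exp(−m). For a negative binomial with k = 1, P(0) = 1/(1+m).

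| Mean | Poisson P(0) | Negative binomial P(0) |
|---|---|---|
| 0.5 | 61% | 67% |
| 1 | 37% | 50% |
| 2 | 14% | 33% |
| 3 | 5% | 25% |
| 5 | 0.7% | 17% |

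The share runs from negligible to most participants. If treatment lowers a Poisson mean of 1 by 30%, P(0) on active is exp(−0.7) = 50% against 37% on placebo. The loss is then unequal between arms and falls more heavily on the arm that does better.

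**2. Effect and power if zeros are dropped.** Gamma-Poisson counts, shape 1.5, true ratio 0.50, 50 per arm, one visit. A t-test on log10 of the non-zero counts is compared with a Wald test of the log rate ratio with robust variance. Here P(0) = (1 + m/1.5)^(−1.5). At a placebo mean of 1 this is 0.465 on placebo and, at mean 0.5, 0.650 on active, so 1 − (0.465 + 0.650)/2 = 44% of participants are kept.

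| Placebo mean | Kept | Ratio read (true 0.50) | Power, log10 | Power, count analysis |
|---|---|---|---|---|
| 1 | 44% | about 0.82 | 24% | 64% |
| 2 | 63% | about 0.73 | 51% | 85% |
| 5 | 83% | about 0.62 | 81% | 95% |
| 10 | 92% | about 0.56 | 90% | 97% |

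Power figures carry a simulation error of a few percentage points. The harm shrinks as counts rise.

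**3. If LOCF fills the gaps.** A zero at follow-up is replaced by an earlier non-zero value, which is by definition worse. With an assumed true endpoint ratio of 0.50 and placebo means of 1, 2 and 3, the geometric-mean ratio reads 0.87, 0.77 and 0.70. These figures also depend on the assumed course of the effect before the endpoint and on the correlation between visits. A zero at baseline has no earlier value, and participants with zeros at every visit stay lost.

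**4. If an offset is used.** With log10(x+1) everyone is kept. At a placebo mean of 1 in the setting of step 2, power is 61% against 64%, so most of the loss is recovered. The ratio is still attenuated. For a true ratio of 0.70 and Poisson control means of 1, 2, 3 and 5:

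- log10(x+1) reads 0.86, 0.80, 0.77 and 0.74;
- dropping zeros reads 0.90, 0.82, 0.76 and 0.70;
- the ratio of raw mean counts, which a count model with log link targets, is about 0.70 throughout.

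**5. Accuracy.** Skewness of simulated beta-binomial accuracy, 42 trials, between-participant SD 8 percentage points:

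| Mean accuracy | Raw | log10 | Arcsine-square-root |
|---|---|---|---|
| 70% | −0.31 | −0.83 | 0.00 |
| 80% | −0.59 | −1.06 | 0.06 |
| 90% | −1.34 | −1.86 | −0.11 |
| 95% | −2.66 | −3.57 | −1.14 |

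Log10 made the skew more negative in every scenario tried (30, 42 or 80 trials; means 65% to 95%).

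**6. Speed.** An assumed lognormal speed goes from a skewness of +0.78 to 0.00. Log10 is suitable there.

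**The case against.** A reader might infer that the trial will discard its best performers on the co-primary measures. The document does not support that, for four reasons.

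- The loss needs zeros to be common, the counts to be among the data transformed, and log10 to be run without an offset. The article states none of these. Its intention-to-treat sentence, which keeps everyone in the final analysis, points away from discarding records.
- It could concern only misses, anticipations and Groton Maze errors. For accuracy and hits zero is not the best score, and speed is not affected.
- Deletion at a single visit is not the plan's route. The plan is a three-visit mixed model with LOCF, so the power figures above illustrate one reading and do not forecast the trial.
- A low mean is the unfavourable case. At a placebo mean of 10 the gap is 90% against 97%, and an offset closes most of it even at a mean of 1.

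It can also be said that a generalised mixed model can carry count or binomial distributions, that distribution and link are ordinary analysis-plan content, and that no effect of the extra accuracy skew on error rates or power has been shown. All of that limits the point.

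What remains is that the article does not merely leave a detail open. It states a rule, applies it to all CogState data and describes the outcomes as continuous, which suggests normalising the data for a Gaussian analysis. An analysis plan would have to override that rule. An offset would repair neither accuracy nor the attenuation of the ratio.

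**Conclusion.** The point holds in a limited form. The stated log10 rule suits mean speed. It is undefined at zero for misses and anticipations, which are listed under the co-primary tests, and for the secondary Groton Maze errors. It makes left-skewed accuracy more skewed.

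Whether the harm is trivial or large cannot be told from the document. Under the assumptions shown, the power shortfall on a count metric with zeros dropped runs from 64 − 24 = 40 percentage points at a placebo mean of 1 to 97 − 90 = 7 at a mean of 10. Attenuation of the ratio runs from marked to slight, and is absent at a Poisson mean of 5. That accuracy is left-skewed is plausible for a percentage capped at 100, but it is also an assumption. The rule should be corrected, because it is stated, reaches metrics listed under the co-primary tests, and costs little to change.

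**What to change.** Replace the blanket rule with a scale fixed per metric, before unblinding:

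- **Mean speed:** log10.
- **Accuracy and hits:** a scale suited to a proportion, for example a binomial-logit model on correct out of total trials, or arcsine-square-root. Close to the ceiling the binomial model is the safer of the two, since at a mean of 95% arcsine-square-root still left a skewness of −1.14.
- **Misses, anticipations and Groton Maze errors:** a count distribution with log link (for example negative binomial) in the generalised mixed model already named, so that zeros stay in as observed values and are never treated as missing.
- **Trigger:** delete the condition that the choice depends on observed non-normality.

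The exact distributions are a matter of judgement. What matters is that each metric has a stated scale and that zeros are kept. The cost is analysis wording only; design, visits, data collection and sample size do not change, and the planned software can fit these models.

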### Sample size for co-primary and secondary outcome measures

This is the first study to utilise Cognition Support Formula® as a treatment for SCI, and thus there are limited comparable studies on which to base a sample size estimation. The most comparable study is by Lim et al. [34], who utilised a similar population (healthy older adults vs. people with MCI vs. AD) and a comparable measure to the current study as outlined in this protocol (CogState® battery). In order to see an improvement in performance in one test of the CogState battery® (group × time interaction) an effect size of Cohen’s *d* = .40 (i.e. Cohen’s *f* = .20, as *d* = 2*f*) at α = .05 was utilised [34].

To detect this effect size of Cohen’s *f* = .20 at α = .05 and 95% power, 100 participants across two groups are required. In order to account for a typical 20% drop-out, a total of 120 participants will need to be recruited (60 participants in the treatment group, and 60 in the placebo group). If the participation rate drops below the estimated number at any point during the course of the study, attempts to recruit additional participants will be made. Sample size may be re-estimated mid-course into the study to ensure adequate power. In this case, data will be unblinded by an objective third party to evaluate the treatment-effect size and power to assist with any potential sample size re-estimation.

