The SHAI is a shortened (18-item) measure of participants’ anxiety pertaining to their health. The highest total score is 52, indicating the highest level of health anxiety. Participants will complete the SHAI at baseline, the midpoint, and the endpoint. A comparison from baseline to endpoint will be made between treatment groups (active and placebo) to determine if health anxiety has decreased with the use of Cognition Support Formula® or placebo.

The FACIT-F is a self-report questionnaire utilised to determine a participant’s level of fatigue during their usual daily activities over the past 7 days. The FACIT-F is a 13-item questionnaire measuring the level of fatigue on a four-point Likert scale. The FACIT-F will be utilised to determine if fatigue and energy levels improve with the use of Cognition Support Formula®.

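### Modelling baseline as a free level of time makes each baseline-to-follow-up treatment contrast a change-score comparison: valid, but less precise than adjusting for baseline

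*Protocol article*

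**What the plan says.** Under Statistical analyses and dissemination, the article specifies "Generalised linear mixed models with a between-subject factor of group (treatment, placebo) and within-subject factor of time (baseline, midpoint, endpoint) will be conducted". It adds: "Planned simple contrasts will be conducted to assess all timepoints (baseline vs. midpoint, midpoint vs. endpoint, and baseline vs. endpoint". It mentions neither a baseline covariate nor a constraint that the arms share a baseline mean. The contrasts are written as pairs of visits; the text does not write them as active minus placebo or say which one is primary. Missing values are filled by last observation carried forward (LOCF), and "All tests will be two-tailed, α = .05".

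The effect of interest is named only in the section Sample size for co-primary and secondary outcome measures, as the "group × time interaction". That section gives no correlation between visits. The only correlation-type figure in the article is the CogState test-retest range of .76 to .93 (intra-class correlation), under Cognitive functioning evaluation. The primary aim, under Rationale and aims, concerns 6 months of treatment.

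**The concern.** In a 1:1 randomised trial the two arms have the same expected baseline score. A model with baseline as a free level of time does not use this: it estimates a separate baseline mean for each arm and subtracts it in full. The baseline-to-endpoint group contrast then carries the sampling noise of both visits, whereas a regression on baseline removes only the part of the noise that baseline predicts. At stake is the precision of the month-6 treatment effect, and with it some power on the co-primary cognitive outcomes. The baseline scores needed for the better analysis are already being collected.

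**Working it through.** **Inputs.** From the article: two arms at 1:1; visits at 0, 3 and 6 months; two-sided α = .05; 100 participants required and 120 recruited; f = .20, which the article equates to d = .40; test-retest .76 to .93. Assumed: a treatment difference of 0.40 SD of the score at a single visit, since the article does not say which SD standardises its d; equal variances across visits; and the test-retest value standing in for the baseline-to-month-6 correlation ρ.

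**The plan's own figure.** The statement is "95% power, 100 participants across two groups are required". For a repeated-measures group-by-time test the noncentrality is λ = f²·N·m/(1−ρ), with m visits. Without ρ the figure cannot be uniquely reproduced. ρ = .5 gives N = 84 (m = 2) or 66 (m = 3). N = 100 comes out at ρ of about .40 with m = 2 (λ = 0.04 × 100 × 2/0.60 = 13.3, power 95.1%), or about .25 with m = 3 (λ = 0.04 × 100 × 3/0.75 = 16, power 95.4%). These are back-solved values, not evidence of the true correlation.

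**The identity.** With complete data, as LOCF produces, the group × endpoint term of the planned model equals the difference in mean change. In one simulated data set (60 per arm, ρ = .76) both were −0.10104. The SE of the term was 0.1156 in the planned model and 0.1081 with a common baseline mean; (0.1081/0.1156)² = 0.87, in line with the formula below.

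**The variance ratio.** Per participant, with unit variance at each visit:

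- change from baseline: 2(1−ρ)
- adjusted for baseline: 1−ρ² = (1−ρ)(1+ρ)
- ratio, adjusted to change: (1+ρ)/2

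At ρ = .76 the ratio is 0.88 (variance −12%, SE about −6%). At ρ = .93 it is 0.965 (variance −3.5%, SE about −1.8%). At an assumed ρ = .5 it is 0.75 (variance −25%).

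**Power.** The SE of the group difference is √(2V/n), with V the variance above and n per arm. The noncentrality is 0.40/SE, on 2n−2 degrees of freedom for change and 2n−3 for the adjusted analysis. For example, at ρ = .76 and n = 50, V is 0.48 against 0.4224, SE 0.1386 against 0.1300, and noncentrality 2.89 against 3.08.

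| ρ | n per arm | change score | baseline-adjusted |
|---|---|---|---|
| .76 | 50 | 81.6% | 86.1% |
| .76 | 60 | 88.0% | 91.7% |
| .93 | 50 | 99.96% | 99.97% |
| .5 (assumed) | 50 | 50.8% | 62.8% |

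The rows with 50 per arm use the number the article says is required. The row with 60 is relevant because LOCF keeps everyone randomised in the analysis.

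**Simulation check.** Over 5000 trials per setting with 60 per arm, the SD of the estimate (change against adjusted) was 0.124 against 0.117 at ρ = .76, and 0.0684 against 0.0676 at ρ = .93.

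**The case against.** The strongest reply is that nothing here is an error. A group-by-time mixed model that includes the baseline visit is a standard, unbiased analysis of a randomised trial, and it matches the interaction named in the sample-size section. That stands: only efficiency is lost. It can be added that covariates are often left to the analysis plan and that this is a condensed article. That stands only in part, because the article is not silent: it fixes the three levels of time. If a fuller plan already adjusts for baseline, the point reduces to aligning the wording.

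The size is also limited. At the article's own coefficients the saving is 3.5% to 12%. LOCF for early drop-outs pulls follow-up values towards baseline, which raises the correlation and shrinks the gain. On the other side, the quoted coefficients are for the battery as a whole, with no test or interval given, so the 6-month correlation on a co-primary measure could be lower. That is an assumption.

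A reader might infer more than the article supports:

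- That efficacy will be judged within arms, because the contrasts are written as visit pairs. The Abstract and the hypothesis under Rationale and aims both set the comparison against placebo, and inside a model crossed with group the contrasts can be read as interaction contrasts. The sentence on the health anxiety inventory likewise opens with a between-group comparison.
- That the treatment effect will be diluted by a group main effect that averages in the pre-treatment visit. The sample-size section points to the interaction, and nothing says the main effect decides efficacy.
- That the whole efficacy test is a change-score test. The identity holds for each single contrast on the scale analysed; the three-visit omnibus interaction is a joint test on 2 degrees of freedom.

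**Conclusion.** The point holds as an inexpensive gain in precision, not as a flaw that threatens validity. Each baseline-to-follow-up treatment contrast in the stated model is a change-score difference, and baseline adjustment would reduce its variance by 12% at ρ = .76 and 3.5% at ρ = .93. For a 0.40 SD difference at ρ = .76 this is worth 4.5 percentage points of power with 50 per arm (86.1 − 81.6) or 3.7 with 60 per arm (91.7 − 88.0), and practically nothing at .93. The larger figure of 25% depends on a correlation of .5 that the article does not give. The results rest on equal variances across visits, complete data after LOCF, and the test-retest range as a stand-in for the 6-month correlation.

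**What to change.** In Statistical analyses and dissemination, replace the three-level time factor by a model of months 3 and 6 with the baseline score as covariate. Alternatively, keep baseline as an outcome in a constrained longitudinal model with one common baseline mean and group-by-time terms for months 3 and 6 only. State the efficacy contrast as active minus placebo at month 6, which follows the 6-month primary aim. Make the change before unblinding. It needs no new data or visits; the cost is analysis wording and one degree of freedom.

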### Current treatments for SCI

Current treatments for older adults with SCI are limited, with most published clinical trials utilising nutraceuticals including soybean-derived phosphatidylserine (SB-PS) and multivitamins containing extracts of *Bacopa monniera* (whole plant) and *Ginkgo biloba* leaf extract [14, 15]. These studies have documented small effects in terms of improvements in cognitive tasks (working memory, recognition memory, and recall) where short trial periods were utilised (12 weeks [14] and 16 weeks [15]). Unfortunately, there is no evidence to determine whether these effects were stable over the trial period (possibly a significant increase, then a tapering off), or whether the cognitive improvements occurred shortly after treatment, or towards the end of the trial period. A longer trial period of 6 months that includes midpoint testing is required to clarify the stability and longevity of any changes. This would prove most fruitful in determining whether such a treatment could manage SCI in the long term.

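### Last observation carried forward is the only stated missing-data method; it can bias the treatment effect and pulls the midpoint-to-endpoint contrast towards no change, although the planned mixed model needs no imputation

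*Protocol article*

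**What the plan says.** Under Statistical analyses and dissemination, the protocol article specifies "Generalised linear mixed models with a between-subject factor of group (treatment, placebo) and within-subject factor of time (baseline, midpoint, endpoint") and adds: "Planned simple contrasts will be conducted to assess all timepoints (baseline vs. midpoint, midpoint vs. endpoint, and baseline vs. endpoint"). It then fixes the handling of missing values: "To handle any missing data, analysis of last observation carried forward will be undertaken within the intention-to-treat analysis model". On scope, "this analysis will be carried out on all five primary and secondary outcome measures of cognition", and on mood and fatigue as well, so both co-primary outcomes are included. The article names no other missing-data method, no assumption about why data are missing and no sensitivity analysis. On testing: "All tests will be two-tailed, α = .05".

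Two other places bear on this. The sample size section plans for losses: "In order to account for a typical 20% drop-out, a total of 120 participants will need to be recruited". The section on current treatments for SCI gives the reason for the midpoint visit: "A longer trial period of 6 months that includes midpoint testing is required to clarify the stability and longevity of any changes".

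**The concern.** Last observation carried forward (LOCF) assumes that a participant's score stays where it was at withdrawal, and it enters that value as if it had been measured. Three consequences matter in this trial.

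- The baseline-to-endpoint effect on the co-primary outcomes can be biased even if drop-out is completely at random and equal in both arms, because an effect that changes after withdrawal is not seen in those who left.
- If drop-out differs by arm and scores drift over time in both arms, LOCF can create a difference where there is none. Its sign depends on the direction of drift and on which arm loses more people, so it cannot be known in advance.
- Anyone lost before month 3 has the baseline value at both later visits, and anyone lost after month 3 has the midpoint value at the endpoint. Both get a midpoint-to-endpoint change of exactly zero. That contrast is the one that should show whether an effect persists or tapers, which is the article's own reason for a six-month design with a midpoint.

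None of this is forced by the intention-to-treat aim. A mixed model fitted by likelihood keeps the observed visits of people who later leave.

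**Working it through.** **Inputs from the article.** 120 participants, 1:1, so 60 per arm; drop-out 20% overall; visits at 0, 3 and 6 months; planning effect 0.40 SD; two-sided α = 0.05; test-retest reliability 0.76 to 0.93, used here as the range for the correlation ρ between visits.

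**Assumptions, not in the article.** Timing of drop-out, its split by arm, the size of any drift common to both arms, and the effect at month 3. The article has no LOCF figure of its own to reproduce.

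**Number affected.** 0.20 × 120 = 24 participants with a forced zero change from midpoint to endpoint.

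**Formula.** Let e be the proportion lost before month 3, l the proportion lost between months 3 and 6, and m3 and m6 the true mean changes from baseline. With drop-out at random within arm, the expected LOCF changes are:

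- baseline to endpoint: (1 − e − l) × m6 + l × m3
- midpoint to endpoint: (1 − e − l) × (m6 − m3)

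**Balanced 20% drop-out, effect growing linearly (0.20 SD at month 3, 0.40 SD at month 6).**

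- Half early, half late: 0.80 × 0.40 + 0.10 × 0.20 = 0.34 SD (15% too small).
- All early: 0.80 × 0.40 = 0.32 SD (20% too small).
- All late: 0.80 × 0.40 + 0.20 × 0.20 = 0.36 SD (10% too small).
- Midpoint to endpoint, whatever the timing: 0.80 × 0.20 = 0.16 SD instead of 0.20 SD.

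Simulation (60 per arm, 4,000 runs, ρ = 0.76, half early and half late) gave 0.341 SD under LOCF with empirical standard error 0.120. The likelihood estimate without imputation was 0.400 SD with standard error 0.139.

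**Balanced 20% drop-out, tapering effect (0.40 SD at month 3, 0.20 SD at month 6).** If all leave late: 0.80 × 0.20 + 0.20 × 0.40 = 0.24 SD, which is too large. The midpoint-to-endpoint change is 0.80 × (−0.20) = −0.16 SD instead of −0.20 SD, so the tapering is understated by a fifth.

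**No effect, common linear drift D, losses half early and half late.** For 30% active versus 10% placebo:

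- active: 0.70 × D + 0.15 × D/2 = 0.775 × D
- placebo: 0.90 × D + 0.05 × D/2 = 0.925 × D
- spurious difference: −0.15 × D

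For 25% versus 15% the same steps give 0.8125 × D − 0.8875 × D = −0.075 × D. Type I error comes from simulated t-tests on LOCF change:

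| Drop-out | Drift D (SD) | Bias (SD) | Type I error |
|---|---|---|---|
| 20% v 20% | 0.4 | 0 | 5.1% (ρ 0.8), 4.5% (ρ 0.93) |
| 30% v 10% | 0 | 0 | 5.1–5.3% |
| 25% v 15% | 0.2 | −0.015 | 5.2–5.4% |
| 25% v 15% | 0.4 | −0.03 | about 6–7% |
| 30% v 10% | 0.2 | −0.03 | 6.1–7.3% |
| 30% v 10% | 0.3 | −0.045 | about 7% (ρ 0.76) to 10% (ρ 0.93) |
| 30% v 10% | 0.4 | −0.06 | about 8–9% (ρ 0.8), 14–15% (ρ 0.93) |
| 30% v 10% | 0.6 | −0.09 | about 13% (ρ 0.8) |

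Reversing the drift, or the arm with more losses, reverses the sign of the bias. The last row was run at ρ = 0.8 only; a higher correlation would raise it. Analyses of the observed data stayed unbiased in these null scenarios, which is expected because drop-out was generated at random within arm.

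**The case against.** The strongest reply is that the harm is conditional and may be small. LOCF raises type I error only when drop-out is unequal and scores also drift; with either one absent it stays at about 5%. The article reports no known practice effects on the cognitive battery, describes decline over years rather than months, and gives no drop-out by arm. A drift of 0.4–0.6 SD is as large as, or larger than, the planning effect itself. If drop-out is equal and the effect is growing, the bias is towards the null, and simulated power at ρ = 0.8 was still 86%.

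Most of this stands and sets the limits of the point. It does not rescue LOCF. The attenuation needs no drift and no imbalance, only an effect that changes after withdrawal. The reassurance that the bias is conservative fails if the effect tapers, which is a pattern the trial is meant to detect. Unequal drop-out is also not far-fetched, since the article reports gastrointestinal upset and insomnia with some of the ingredients, although it calls these minor or mild.

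A reader might infer more than the article supports:

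- *That the stability contrast is fixed at zero for the trial.* It is zero only for participants with missing visits; at 20% drop-out the contrast shrinks by about a fifth.
- *That LOCF is always biased under random drop-out.* With equal drop-out and no effect it is not.
- *That the estimate, its standard error and the stability conclusion are bound to be wrong.* This is not shown. The LOCF standard error is smaller because imputed zero changes add no variance, yet with equal drop-out the test kept its level.
- *That the mixed model is safe whatever the cause of drop-out.* If people leave because of unobserved decline, it can be biased too.

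**Conclusion.** The point holds in conditional form. The article fixes LOCF as the only handling of missing values for both co-primary outcomes and the other cognition, mood and fatigue outcomes. This is a stated choice, not a detail left to an analysis plan that is not shown, and the article gives no reason why scores should stay flat after withdrawal.

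Under balanced 20% drop-out and a linearly growing effect, the cost is 10–20% of the endpoint effect and 20% of the midpoint-to-endpoint effect. The false-positive risk ranges from none to about 15% in the scenarios of 30% versus 10% drop-out with 0.4–0.6 SD drift; the upper end needs marked imbalance, large drift and high correlation between visits. All these sizes depend on assumed timing, imbalance and drift, because the article gives only the overall 20%. What does not depend on them is that LOCF is unnecessary here and that each participant lost after baseline contributes an imputed zero to the contrast meant to show stability or tapering.

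**What to change.** Remove LOCF as the primary handling of missing data. State that the planned mixed model will be fitted by likelihood to all observed visits of all randomised participants, an analysis that is valid if data are missing at random. Add a sensitivity analysis for departures from missing-at-random; its form, like the covariance structure, can be set in the statistical analysis plan. If LOCF is kept for comparison with earlier studies, label it as a supplementary analysis only.

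The cost is a change of wording and a little programming, with no new data. The change should be made and dated before anyone sees outcome data by arm.
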